**6.6 Concomitant medications:**

- To prevent vomiting in the combination group, intravenous H3 receptor antagonists with or without dexamethasone is routinely used to stop vomiting before each course of chemotherapy, and NK-1 inhibitors (aprepitant) can also be given.
- To prevent the occurrence of anaphylaxis, diphenhydramine 20 mg is routinely administered intramuscularly 30 minutes before cetuximab chemotherapy.
- The investigator may give G-CSF support according to the patient’s bone marrow adverse reactions. However, G-CSF is not recommended for the first prophylactic treatment.

Other concomitant medications may be determined by the investigator on a patient-by-patient basis.

**7. Efficacy evaluation**

**7.1 Indicators of effectiveness evaluation**

All enrolled patients (intent-to-treat population) will be analyzed for efficacy. The indicators of efficacy evaluation of this study include:

- ORR (partial response (PR) plus complete response (CR)): assessed by the investigator using RECIST v1.1 criteria.
- DpR: the investigator assesses DpR by measuring the ratio of maximum tumor regression to baseline tumor, and calculates the median value.
- R0 resection rate: defined as the proportion of patients who achieve complete resection (pathologically defined R0 resection) after treatment with cetuximab plus FOLFOXIRI regimen or cetuximab plus FOLFOX regimen according to the study protocol.
- ETS: target lesion reduction of a least 20% from the nadir following 4 treatment courses assessed using the RECIST version 1.1 criteria
- PFS: assessed by the investigator using RECIST v1.1, defined as the time from the start of study treatment to disease progression, or relapse after resection of liver metastases, or death due to any cause.
- OS: defined as the time from the start of study treatment to death due to any cause.

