### 2.2 Secondary objectives

- Depth of response (DpR)
- R0/resection rate
- Early tumor shrinkage (ETS)
- Progression-free survival (PFS) of the whole group
- OS in the whole group
- Safety (adverse reactions of chemotherapy, surgical complications, etc.)

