## 9. Assessment during the study

## 9.1 Pre-chemotherapy assessment

The following assessments will be performed during each course:

- Concomitant medication
- Clinical data: weight, physical examination, vital signs, ECOG performance score
- Laboratory tests: hematology, biochemistry (including ALP) and tumor markers on Day 0 and Day 14
- EKG
- Tumor assessment:

Assessments will be performed every 4 courses and the number of examinations may be increased if necessary.

Tumor measurements/assessments are performed using CT or MRI scans based on RECIST v1.1 criteria.

For each patient, the same assessment method should be used throughout the study, and the assessment should be performed by the same assessor as far as possible.

All metastases detected at baseline screening should be assessed at every tumor assessment.

- MDT assessment:

Every 4 courses, the number of assessments may be increased if necessary.

In this study, 8 (no less than 6) courses of conversion chemotherapy are recommended, and some patients also need to appropriately prolong the treatment course before hepatectomy with or without radiofrequency treatment is considered.

This is mainly because that this study includes patients with unresectable colorectal liver metastases, who usually have a large number of liver metastases, large lesions, with high-risk CRS score. Current clinical practice recommends surgical resection after adequate chemotherapy to achieve more benefit.

- Chemotherapy related adverse events
- Survival

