*Lymph nodes* merit special mention since they are normal anatomical structures that may be visible by imaging even if not involved by tumor. As noted in Section 3, pathological nodes which are defined as measurable and may be identified as target lesions must meet the criterion of a short axis of P15 mm by CT scan. Only the *short* axis of these nodes will contribute to the baseline sum. The short axis of the node is the diameter normally used by radiologists to judge if a node is involved in a solid tumor. Nodal size is normally reported as two dimensions in the plane in which the image is obtained (for CT scan, this is almost always the axial plane; for MRI, the plane of acquisition may be axial, sagittal, or coronal). The smaller of these measures is the short axis. For example, an abdominal node which is reported as being 20 mm · 30 mm has a short axis of 20 mm and qualifies as a malignant, measurable node. In this example, 20 mm should be recorded as the node measurement (See also the example in Fig. 4 in Appendix II). All other pathological nodes (those with short axis P10 mm but <15 mm) should be considered non-target lesions. Nodes that have a short axis <10 mm are considered non-pathological and should not be recorded or followed.

A *sum of the diameters* (longest for non-nodal lesions, short

axis for nodal lesions) for all target lesions will be calculated and reported as the *baseline sum diameters*. If lymph nodes are to be included in the sum, then as noted above, only the *short* axis is added to the sum. The baseline sum diameters will be used as a reference to further characterize any objective tumor regression in the measurable dimension of the disease.

All other lesions (or sites of disease), including pathological lymph nodes, should be identified as *non-target lesions* and should also be recorded at baseline. Measurements are not required and these lesions should be followed as ‘present’, ‘absent’, or in rare cases, ‘unequivocal progression’ (more details to follow). In addition, it is possible to record multiple non-target lesions involving the same organ as a single item on the case record form (e.g., ‘multiple enlarged pelvic lymph nodes’ or ‘multiple liver metastases’).

- 1. **Response criteria**

This section provides the definitions of the criteria used to determine objective tumor response for target lesions.

- - 1. **Evaluation of target lesions**

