Complete Response (CR): Disappearance of all target lesions. Any pathological lymph nodes (whether target or non-target) must have a reduction in short axis to

<10 mm.

Partial Response (PR): At least a 30% decrease in the sum of diameters of target lesions, taking as reference the baseline sum diameters.

Progressive Disease (PD): At least a 20% increase in the sum of diameters of target lesions, taking as reference the *smallest sum obtained in the study* (this includes the baseline sum if that is the smallest in the study). In addition to the relative increase of 20%, the sum must also demonstrate an absolute increase of at least 5 mm. (*Note:* the appearance of one or more new lesions is also considered progression).

Stable Disease (SD): Neither sufficient shrinkage to qualify for PR nor sufficient increase to qualify for PD, taking as reference the smallest sum diameters while in this study.

- - 1. *Special notes on the assessment of target lesions Lymph nodes.*

Lymph nodes identified as target lesions should always have the actual short axis measurement recorded (measured in the same anatomical plane as the baseline examination), even if the nodes regress to below 10 mm during the study. This means that when lymph nodes are included as target lesions, the ‘sum’ of lesions may not be zero even if complete response criteria are met since a normal lymph node is defined as having a short axis of <10 mm. Case report forms or other data collection methods may therefore be designed to have target nodal lesions recorded in a separate section where, in order to qualify for CR, each node must achieve a short axis <10 mm. For PR, SD, and PD, the actual short-axis measurement of the nodes are to be included in the sum of target lesions.

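### Early tumour shrinkage is measured from the nadir instead of baseline, so a patient with an extra early scan can be wrongly counted as having no ETS

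*Protocol*

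**What the plan says.** Section 2.2 lists ETS among the secondary objectives, without ranking them. Section 7.1 gives the only definition: "target lesion reduction of a least 20% from the nadir following 4 treatment courses", to be judged by RECIST 1.1.

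Appendix IV, which reproduces RECIST 1.1, uses two different references:

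- **Regression is measured from baseline.** The general statement is "The baseline sum diameters will be used as a reference to further characterize any objective tumor regression in the measurable dimension of the disease". Partial response follows it: "At least a 30% decrease in the sum of diameters of target lesions, taking as reference the baseline sum diameters".
- **Progression is measured from the smallest sum on study.** The rule is "At least a 20% increase in the sum of diameters of target lesions, taking as reference the" smallest sum obtained, with the clarification "this includes the baseline sum if that is the smallest in the study".

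Depth of response, defined two items above ETS in Section 7.1, relates maximum regression to the baseline tumour.

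On timing, Section 9.1 states: "Assessments will be performed every 4 courses and the number of examinations may be increased if necessary". Section 5.2 repeats the regimen every 14 days, so 4 courses take about 4 × 14 = 56 days, or 8 weeks. The first scheduled on-treatment scan is therefore the one on which ETS is judged.

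**The concern.** A reduction is naturally measured from the starting value. The nadir is the low point from which regrowth is judged, and that is the only use Appendix IV makes of the smallest sum when it defines progression. The ETS definition calls on RECIST 1.1 and then pairs a reduction with the progression reference. The 20% figure also appears in the progression rule, so that reference may have been carried over by mistake. That origin is an inference; the conflict between the two places is on the page.

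At stake is the ETS classification of individual patients, and through it the ETS rate in each arm. With the nadir as reference, the result can depend on how often a patient was scanned and not only on how far the tumour shrank. Extra scans are at the investigator's discretion, the trial is open-label and response is investigator-assessed, so the reference should not be open to interpretation once measurements are known.

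**Working it through.** **The plan's own figures.** The protocol gives no expected rate, power or sample size for ETS, so there is no ETS figure to reproduce. The only sample-size figure is for the primary endpoint (Section 4): 80% against 60%, two-sided α of 10%, power 80%, 128 patients. With pooled variance and no continuity correction,

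n per arm = [1.645 × √(2 × 0.70 × 0.30) + 0.842 × √(0.80 × 0.20 + 0.60 × 0.40)]² / 0.20² ≈ 63.9, rounded up to 64, or 128 in total.

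This matches the protocol, and ETS does not enter the calculation.

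**Inputs for ETS.** Threshold: 20% (Section 7.1). Reference: baseline sum (Appendix IV, regression) or nadir (Section 7.1). Scans: one scheduled after 4 courses, with extra ones allowed (Section 9.1). The protocol holds no patient measurements, so the diameters below are illustrative.

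**Formula.** Percentage reduction = (reference − course-4 sum) / reference. ETS is met at 20% or more.

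| Sums in mm (baseline → extra scan, if any → course 4) | From baseline | From smallest earlier sum | From smallest sum including the course-4 scan |
|---|---|---|---|
| 100 → 79 | 21.0% (yes) | 21.0% (yes) | 0% (no) |
| 100 → 75 → 70 | 30.0% (yes) | 6.7% (no) | 0% (no) |
| 100 → 75 → 65 | 35.0% (yes) | 13.3% (no) | 0% (no) |
| 100 → 85 → 70 | 30.0% (yes) | 17.6% (no) | 0% (no) |
| 100 → 60 → 60 | 40.0% (yes) | 0% (no) | 0% (no) |

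For the second row: (100 − 70)/100 = 30.0%; (75 − 70)/75 = 6.7%; (70 − 70)/70 = 0%.

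**Smallest earlier sum, scheduled scan only.** The only earlier sum is baseline, so the two definitions agree (first row).

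**Smallest earlier sum, with an extra scan before course 4.** Let B be the baseline sum, E the extra-scan sum and C the course-4 sum. If E is not below B, baseline remains the smallest earlier sum and nothing changes. If E is below B, the baseline rule requires C ≤ 0.80 × B and the nadir rule requires C ≤ 0.80 × E, which is stricter. The patient is misclassified when 0.80 × E < C ≤ 0.80 × B. With B = 100 and E = 75, that is 60 < C ≤ 80 mm. The error runs one way only: true shrinkers are counted as no ETS, never the reverse.

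**Smallest sum including the current scan.** The reference can never exceed C, so the reduction can never exceed 0% and the 20% threshold cannot be met.

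**The case against.** The strongest defence is that the ordinary patient is unaffected. The ETS scan is the first scheduled on-treatment scan, and Appendix IV counts baseline among the sums from which the smallest is taken. This stands: for anyone without an extra scan before course 4, the smallest earlier sum is baseline and the classification is correct.

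A reader might infer that the endpoint is impossible to reach and that ETS will be 0% in both arms. That follows only if the course-4 scan is compared with itself, which defeats the purpose of the definition and which an analyst is unlikely to do. The definition also refers to RECIST 1.1, and the appendix names baseline as the reference for regression, so the intended meaning can be recovered. The reading shows that the wording is unsound; it does not predict the result.

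A reader might also infer bias between the arms. The protocol gives no frequency for extra scans and nothing to suggest that they will differ by arm, so this is a possibility and not a demonstrated bias.

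Finally, ETS is one of several unranked secondary endpoints and has no part in the sample size. This also stands, and it limits the importance of the point. None of these arguments makes the nadir the right reference: the definition gives the intended answer only when the nadir happens to equal baseline.

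**Conclusion.** The concern holds as an error of definition in Section 7.1. The stated reference conflicts with the baseline reference for regression in Appendix IV and with depth of response in the same list, and no other section corrects it. This is a rule stated wrongly, not a detail left to the statistical analysis plan: a plan that used baseline would contradict the protocol, and one that copied the protocol would carry the error forward.

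Its size is limited. Taking nadir as the smallest earlier sum, misclassification is confined to patients who have an extra scan within roughly the first 8 weeks, whose sum is already below baseline at that scan, and whose course-4 sum falls between 80% of the extra-scan sum and 80% of baseline. Their number is unknown, so the effect on the ETS rate cannot be calculated. The documents do not support saying that the whole ETS rate is wrong. The primary response-rate analysis, the 128 patients required and the 140 planned are untouched.

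**What to change.** In Section 7.1, replace the nadir as the ETS reference with the baseline sum of diameters of target lesions, and keep the 20% threshold and the assessment after 4 treatment courses. ETS is then met when the course-4 sum is at most 80% of the baseline sum, whether or not other scans were done earlier.

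The cost is one phrase in the protocol, to be changed before ETS is analysed. Appendix IV already requires target-lesion measurements at baseline and at each later evaluation, so no new scans, data or patients are needed. The fault shown here does not call for any change to the timing of the assessment or a new rule for missing scans; the latter is commonly left to the statistical analysis plan.

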**10. Statistical analysis**

**10.1 Study population**

The analysis population of this study includes full analysis set (FAS), per protocol set (PPS) and safety set (SS). The principle of **intention-to-treat (ITT) population** refers to the principle that the analysis is performed according to the original randomized intention, that is, the analysis should include all randomized subjects, and the subjects assigned to any treatment group should be followed up, evaluated and analyzed as members of this group, regardless of the actual treatment received.

**FAS** is defined as the set of data obtained after the least and fairest elimination of data from all subjects, which is as close as possible to the ideal according to the ITT principle.

**PPS** is a subset of FAS whose subjects are sufficiently compliant with the protocol and can be assessed for the effect of treatment and whose characteristics meet the following principles: (1) completion of predetermined treatment; (2) measurability of primary study endpoints; (3) absence of major protocol violations, including violations of the eligibility criteria. If the PP population reaches more than 95% of ITT population, the analysis of PP population is not necessary.

**SS** includes all patients who participate and receive at least one dose of the investigational drug, and if the participating population is not consistent with the as-treated population, the safety analysis population will be based on the as-treated population.

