**2.6. Confirmatory measurement/duration of response**

**2.6.1**. Confirmation

In non-randomized trials where response is the primary end-point, confirmation of PR and CR is required to ensure responses identified are not the result of measurement error. This will also permit appropriate interpretation of results in the context of historical data where response has traditionally required confirmation in such trials (see the paper by Bogaerts et al. in this Special Issue[^10^](#_bookmark12)). However, in all other circum- stances, i.e., in randomized trials (phase II or III) or studies where stable disease or progression are the primary end-points, confirmation of response is not required since it will not add value to the interpretation of trial results. However, elimination of the requirement for response confirmation may increase the importance of a central review to protect against bias, in particular in studies that are not blinded.

In the case of SD, measurements must have met the SD criteria at least once after study entry at a minimum interval (in general not less than 6–8 weeks) that is defined in the study protocol.

- - 1. **Duration of overall response**

The duration of overall response is measured from the time measurement criteria are first met for CR/PR (whichever is first recorded) until the first date that recurrent or progressive dis- ease is objectively documented (taking as reference for progressive disease the smallest measurements recorded in the study).

The duration of the overall complete response is measured from the time measurement criteria are first met for CR until the first date that recurrent disease is objectively documented.

- - 1. **Duration of stable disease**

Stable disease is measured from the start of the treatment (in randomized trials, from the date of randomization) until the criteria for progression are met, taking as reference the *smallest sum in the study* (if the baseline sum is the smallest, this is the reference for calculation of PD).

The clinical relevance of the duration of stable disease varies in different studies and diseases. If the proportion of patients achieving stable disease for a minimum period of time is an end-point of importance in a particular trial, the protocol should specify the minimum time interval required between two measurements for determination of stable disease.

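### PFS and OS are timed from first dose although the protocol declares an intent-to-treat population, so a randomised patient who is never dosed has no survival time

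*Protocol*

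**What the plan says.** Section 7.1 opens its list of efficacy measures with the population: "All enrolled patients (intent-to-treat population) will be analyzed for efficacy". PFS and OS are both in that list. OS is given as "OS: defined as the time from the start of study treatment to death due to any cause". The other survival endpoint has the same origin: "PFS: assessed by the investigator using RECIST v1.1, defined as the time from the start of study treatment to disease progression", with postoperative recurrence and any death also counted as events.

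Section 10.1 states the intent-to-treat principle: "the analysis should include all randomized subjects, and the subjects assigned to any treatment group should be followed up, evaluated and analyzed as members", each in the arm assigned and whatever treatment was actually given. The full analysis set is then described as "the set of data obtained after the least and fairest elimination of data from all subjects", as near to that principle as possible. The safety set is defined separately, by receipt of study drug. Section 10.2 compares survival between the arms with a log-rank test stratified by the randomisation factors.

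In Section 5.1, randomisation (step 4) follows the multidisciplinary resectability meeting (step 3) and precedes treatment. The protocol summary describes the trial as open-label.

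**The concern.** The population and the time origin do not fit together. The population is everyone randomised; the clock starts at an event that some of them may never reach. A patient who declines after learning the allocation, deteriorates, or dies before the first infusion belongs to the declared population but has no time zero. An event between randomisation and first dose is not counted either.

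What is at stake is the protection that randomisation gives to the two survival comparisons. Allocation is known before dosing, and the protocol's own background section says that triplet chemotherapy is more toxic and less well tolerated than a doublet. If more patients failed to start in one arm, and their prognosis differed from the rest, a comparison of starters only would be biased. A larger sample would not remove that bias.

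**Working it through.** **1. The plan's own figure.** Section 4 gives ORR 80% against 60%, two-sided alpha 10%, power 80%, and 128 patients. With pooled variance under the null and no continuity correction:

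n per arm = [1.645 × √(2 × 0.7 × 0.3) + 0.842 × √(0.8 × 0.2 + 0.6 × 0.4)]² / 0.2² = (1.066 + 0.532)² / 0.04 = 63.9, so 64 per arm and 128 in total.

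The figure reproduces exactly. It rests on a proportion, so no time origin enters it. A never-dosed patient can stay in the ORR denominator without a start date. The protocol gives no event count or power for PFS or OS.

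**2. The passages side by side.**

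| Element | Where | Who or when |
|---|---|---|
| Efficacy population | 7.1 | all enrolled, labelled intent-to-treat |
| Meaning of enrolled | 4 | patients entered into randomisation, 70 per arm |
| Intent-to-treat principle | 10.1 | all randomised, whatever they received |
| PFS and OS time zero | 7.1 | start of study treatment |
| Survival test | 10.2 | stratified log-rank between randomised arms |
| Fallback origin for the never-dosed | none | not given |

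The first three rows and the fourth cannot all be applied to a patient who is randomised and not treated. The protocol allows for such patients, since it defines the safety set by exposure and separately from the randomised population.

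**3. How many patients.** The number with a time zero is 140 minus the number who never start. No rate is given. Assumed values: 1% is 1.4, 2% is 2.8, 5% is 7 and 10% is 14 patients. The illustrative 2-5% is therefore about 3-7 patients.

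**4. The shift for patients who are dosed.** Section 8 places screening within 28 days before treatment, and the multidisciplinary assessment on Day -7 to -1. Randomisation needs that assessment, because unresectability is an eligibility criterion and resectability category is a stratification factor. A patient handled to protocol is thus randomised at most about 7 days before first dose, and at most 28 on the widest reading. Against the 5-year median follow-up in Section 10.3 (1,825 days) that is 7/1825 = 0.4%, or 28/1825 = 1.5%.

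**5. Illustration of possible bias.** The assumptions here are not in the protocol: true hazard ratio 1, median OS 36 months, cut-off at 60 months, 70 per arm, 400 simulated trials per row. Both arms contain the same share of patients with 2 or 4 times the hazard. In one arm they do not start and drop out; in the other they all start.

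| Non-starters in one arm | Hazard multiple | Mean HR, starters only | Mean HR, all randomised | Ratio |
|---|---|---|---|---|
| 2 (3%) | 2 | 0.979 | 0.999 | 0.98 |
| 2 (3%) | 4 | 0.952 | 0.982 | 0.97 |
| 4 (5%) | 2 | 0.958 | 0.995 | 0.96 |
| 4 (5%) | 4 | 0.956 | 1.017 | 0.94 |
| 7 (10%) | 2 | 0.953 | 1.018 | 0.94 |
| 7 (10%) | 4 | 0.890 | 0.993 | 0.90 |

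The chance of an event by 60 months at base hazard is 1 − 2^(−60/36) = 0.685, so about 96 events in 140 patients. The standard error of the log hazard ratio is about 2/√96 = 0.20 in one trial and 0.20/√400 = 0.01 for a mean of 400. The spread of 0.98-1.02 in the all-randomised column is therefore simulation noise. The ratio column is steadier, because both estimates come from the same simulated data. If all 3-7 illustrative patients fell in one arm, that would be 4-10% of it, roughly the last four rows: a shift of about 4-10%.

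**The case against.** The strongest reply is that little depends on this. PFS and OS are secondary, nothing in the design is sized on them, and the shift for treated patients is about a week in both arms. All of that stands, and it sets the severity.

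It can also be said that the protocol nowhere states that never-dosed patients leave the log-rank test, and that the full analysis set allows minimal exclusions. Both are true. Exclusion follows from the missing origin and is not written as a rule, and the conflict is sharper with Section 7.1 than with Section 10.1. But a patient without a time zero cannot enter the test, and an analysis plan could supply one only by departing from the protocol's definition.

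The remedy also recovers less than a head count suggests. Section 9.4 bars follow-up after consent is withdrawn, so a patient who refuses the allocation and withdraws would be censored near day 0 even when timed from randomisation. The real gain is in non-starters who keep their consent and in those with an event before dosing.

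Three stronger readings are tempting and are not supported:
- A reader might infer that the gap between randomisation and first dose is unlimited, since no maximum is stated directly. The Section 8 windows limit it.
- A reader might take Appendix IV as contradicting Section 7.1. Its phrase "in randomized trials, from the date of randomization" concerns duration of stable disease, which is not an endpoint here. The appendix gives no origin for PFS, so this is support by analogy only.
- A reader might conclude that the survival results will be biased. Neither the non-starting rate nor any difference between arms is documented.

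**Conclusion.** The definitions are wrong as written. Section 7.1 declares an intent-to-treat population and gives PFS and OS an origin that not every member of it has. As the text stands, the survival comparison can cover only patients who started treatment.

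The practical size is probably small. On an assumed 2-5% it concerns about 3-7 of 140 patients. With all of them in one arm and a markedly worse prognosis, the illustration moves the hazard ratio by about 4-10%. That is well inside the uncertainty of one trial of this size: with a standard error of 0.20 on the log scale, the 95% limits around 1 are about 0.67 to 1.49. With few non-starters, or balanced numbers, the effect is close to nil.

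Severity is should-fix. ORR and the 128/140 calculation are untouched, and a reader who took this as a threat to the primary result would be going beyond the documents.

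**What to change.** In Section 7.1, change the origin of both PFS and OS to the date of randomisation, and say that this applies to all randomised patients. Time from first dose may be kept, at most, as a sensitivity analysis among those treated; the safety set needs no change. It would also help to report by arm how many patients were randomised but never treated, and how many of those withdrew consent, so that readers can judge whether the choice mattered.

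The cost is one phrase in each of two definitions. Section 4 says the web-based randomisation system records every randomisation, so no new data are needed. The sample size, the primary analysis and patient management stay as they are. The change should be in place before the survival data are analysed.
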